# MSSM Protocol Template HRP-503a

| Instructions:   1. Prepare a document with the following sections. Note that, depending on the nature of your research, certain sections below may not be applicable. Indicate N/A as appropriate, explaining where possible. 2. For any items described in the sponsor’s protocol, grant application or other source documents submitted with the application, you may reference the title and page numbers of these documents rather than cutting and pasting into this document. **Do NOT refer to any derived documents, such as the Sample Consent document, or other internal documents required with the submission.** 3. If you reference page numbers, attach those pages to this protocol. 4. When you write a protocol, keep an electronic copy. You will need to modify this copy when making changes. |
| --- |

**Brief Summary of Research (250-400 words):**

Gut microbes can influence numerous aspects of human biology. Alterations in the function and composition of gut microbial flora (gut microbiota) have been linked to inflammatory bowel disease, chronic inflammation, dyslipidemia, diabetes mellitus, atopic disorders, cardiovascular disease, neoplasms, and obesity. Diet and other environmental factors have been found to alter the gut microbiome, and recent studies have shown that gut microbiota is altered in patients with end stage renal disease (ESRD) who are receiving renal replacement therapy (hemodialysis). However, little is known on whether the alteration in gut microbiota seen in renal patients is due to uremia. Several lines of evidence suggest that renal failure alters the chemical environment of the intestinal lumen which could impose a selective pressure on the growth of certain gut microbes, or is an epiphenomenal finding due to the complex confounding factors. This alteration in the gut microbiota of patients with renal failure significantly impacts the development of co-morbid conditions such as accelerated atherosclerosis, abnormal bone mineral metabolism, and chronic inflammation that are associated with renal failure. We hypothesize that the gut microbiota of patients with ESRD is highly diet dependant, and that changing the diet to a low advanced glycation end products (AGEs) diet will result in a better microbial composition and characteristics in the gut of patients with ESRD on peritoneal dialysis (PD).

1. Objectives:

*Research Question:*

- 1. How does a diet low or high in Advanced Glycation End products (AGEs) change the composition and activity of gut microbiota in patients with ESRD on PD?
  2. Will these changes in gut microbiota affect the serum levels of AGEs along with other inflammatory markers?
  3. Can a diet low in AGEs be associated with improvement in gut microbiota and therefore improve markers of chronic inflammation in ESRD patient?

The purpose of this study is to find out if a diet low in Advanced Glycation End products (Low-AGE diet) can improve the composition and diversity of gut bacteria in people with ESRD on PD.

1. Background

- A wide range of systemic diseases affects the kidney to cause chronic kidney disease (CKD) and end stage renal disease (ESRD), including autoimmune, metabolic and genetic diseases. Loss of kidney function in CKD/ESRD is associated with deleterious alterations in physiological and metabolic functions; uremic toxins are involved in the development of cardiovascular disease and progression of renal disease in CKD. While it is known that there is accumulation of bodily waste that is not excreted in individuals with renal failure, little has been done to delineate the production of uremic toxin, which are mainly produced by gut microbes and then absorbed from the gut into the bloodstream.
- Studies have shown that gut microbes can influence numerous aspects of human biology, and alterations in the function and composition of gut microbial flora (microbiota) play a major role in the pathogenesis of diverse human illnesses such as chronic inflammation, diabetes mellitus, and cardiovascular diseases. Gut microbes provide protection against pathogenic organisms, contribute to energy metabolism, serve a clear role in the development and modulation of the human gut immune system, and participate in nitrogen and micronutrient homeostasis by synthesizing amino acids and various vitamins. However, whether the composition of gut microbes is altered in humans with renal failure has not been clearly demonstrated. Furthermore, whether alterations in the gut microbiota due to renal failure contribute to development of co-morbid conditions associated with CKD has never been examined.
- By-products of protein and amino acid catabolism are known to contribute to medical conditions. For example, gut microbe-mediated protein catabolism produces P-cresol from tyrosine and phenylalanine , and indole from tryptophan which later is converted by the liver to indoxyl sulfate. P-cresol sulfate and indoxyl sulfate are considered uremic toxins because they contribute to adverse cardiac outcomes and serum levels of these compounds are elevated in patients with advanced kidney disease.
- There are several lines of evidence to suggest that the gut microbiota is likely altered in patients with CKD. It has been established that protein assimilation in the small intestine is impaired in CKD . As a consequence, an increased amount of dietary protein becomes available to the colon. The reduction in the ratio of available carbohydrate to protein in the colon may favor a shift from the more favorable saccharolytic to proteolytic fermentation pattern resulting in increased ammonia production. High levels of ammonia are responsible for elevated pH, which foster overgrowth of proteolytic species. In addition, colonic transit time is prolonged in CKD . As a result of increased transit time, a larger part of the colon becomes carbohydrate-deprived, which will induce an expansion of proteolytic species . A distinct gut microbiome with decreases in saccharolytic bacteria ( Lactobacillaceae and Prevotellaceae families) have been associated with CKD .
- Advanced Glycation End products (AGEs) are formed via the Maillard reaction, which consists of a complex network of non-enzymatic reactions involving the carbonyl groups of reducing sugars which react with the amino groups of proteins . AGEs are generated in vivo as a normal consequence of metabolism, but their formation is accelerated under conditions where blood glucose is chronically elevated such as poorly controlled diabetes . AGE formation is also increased in the presence of oxidative stress, which is frequently observed in individuals with the metabolic syndrome and diseases such as ESRD .
- AGEs affect mitochondrial function and results in the production of reactive oxygen species (ROS) . They also promotes the activation of several transcription factors including nuclear factor kappa-B (NF-κB), with subsequent upregulation of chemokines, such as MCP-1 and profibrogenic mediators such as TGFβ in addition to proinflammatory cytokines which are known to be involved in thrombogenesis, vascular inflammation and pathological angiogenesis. These AGE receptor- mediated events contribute to many of the long-term complications of diabetes and other diseases . AGE/AGE-receptor ligation also promotes overproduction of ROS which can then activate NF-κB, a key driver of inflammation .
- It is thought that certain dietary AGEs are largely undigested by human gut enzymes and eventually enter the colon, where they may act as a growth substrate for detrimental bacteria such as some Clostridium and Bacteroides species . Therefore it is conceivable that individuals who consume highly processed diets (which contain large quantities of AGEs) may adversely alter their colonic microbial composition, potentially enhancing their risk for the development of metabolic diseases such as obesity and type 2 diabetes .
- The purpose of this study is to find out if a diet low in Advanced Glycation End product (Low-AGE diet) can improve the composition and diversity of gut bacteria in patients with ESRD on PD.

1. Setting of the Human Research

This is a pilot study. All research procedures will be performed at Icahn School of Medicine at Mount Sinai. Potential study participants will be evaluated at Peritoneal Dialysis Unit:

Entrance:       [name]

(Klingenstein Clinical Center (KCC) Building)

Peritoneal Dialysis Unit (PDU): Annenberg Building, MC level, room 403 (Nursing Station)

[contact]

*Patients with ESRD receiving PD at Icahn School of Medicine at Mount Sinai will be invited by their primary care nephrologist ([name]) to participate in the study.*

No involvement of any community advisory board for research conducted outside of MSSM.

1. Resources Available to Conduct the Human Research

We have a clinical research team made up of [name], PI; [name], Co-Investigator; [name], Co-Investigator; [name], Co-Investigator; [name], Senior Clinical Research Coordinator; and Dietitian, [name], RD, CDE.

At the beginning of this study, Standard Operating Procedure (SOP) will be established to ensure that all individuals involved in the study know the study procedures. Each member of the team will be adequately informed about the protocol, the investigational plans in reference to the AGE diet and their trial-related duties and functions.

1. Study Design
   1. Recruitment Methods

Potential participants will be identified and recruited from the Peritoneal Dialysis Unit. Patients with ESRD on PD and receiving treatment at Mount Sinai Hospital will be identified from the PD patient list.

All patients identified will receive a letter of invitation by mail informing them about the research project and inviting them to participate in the study. Two weeks after the invitation, the study team will contact the candidates by phone and explain the study protocol in detail, answer their questions and formally invite them to participate.

If the candidate agrees to participate in the study, a face-to-face interview will be scheduled. During this interview the investigators will explain the study design and intervention to the candidate, and if the candidate agrees to participate in the study, he/she will be asked to sign the informed consent form. Subjects will then be screened for inclusion/exclusion criteria and determined to be eligible or not for the study at that point. (Please refer to section d: Study timeline for details)

*We will also post the study on ClinicalTrials.gov website.*

- 1. Inclusion and Exclusion Criteria

Inclusion criteria:

- Age > 18 years.
- Patients with ESRD on PD.
- Patients are able to understand and give consent.
- Patients with estimated daily dietary AGE intake > 12 AGE Eq/day (12,000 kiloUnits/day) based on 3-day food records.

Exclusion criteria:

- History of diabetes mellitus.
- Patient on antibiotics in the last three months.
- Liver cirrhosis, and heart failure with EF < 30%.
- The use of chemotherapy, immunosuppressive medications, probiotics, and steroid in the last month.
- Oral iron supplementation in the last month.
- History of small or large intestine resection or small bowel obstruction.
  1. Number of Subjects

A minimum of 30 participants (15 in each group) is required. Based on previous experience, we expect a 20% drop out and extrapolate that an initial enrollment of 30 participants (15 in each group) will be sufficient to achieve at least 10 participants in each group at study end.

This is a pilot study. There are no prior studies evaluating the effects of dietary AGEs on gut microbiota in normal subjects or patients with different disease including kidney diseases. Thus the investigators cannot perform power analysis and sample size calculation. Based on our prior experience and recruitment rate and drop off noted when conducting a similar study we believe that 20 patients divided in two groups is a feasible and obtainable sample size.

Subjects will be divided in two groups:

- G1: 15 patients will continue their original diet.
- G2: 15 patients will be instructed to initiate a low AGE diet.
  1. Study Timelines

The duration anticipated to enroll all study subjects is 12 months after the IRB approval.

Participants will be enrolled in the study and followed for one month.

Study timeline will be divided to 4 steps.

All study visits will be held at Peritoneal Dialysis Unit (PDU):

Entrance:       [name]

(Klingenstein Clinical Center (KCC) Building)

Peritoneal Dialysis Unit : Annenberg Building, MC level, room 403 (Nursing Station)

[contact]

**Step 1: Candidates identification:**

Invitation: All patients with ESRD on PD in the peritoneal dialysis unit will receive a letter of invitation and diet log sheet (forms attached).

Phone call 1 (15-30 minutes): Two weeks after sending the letters of invitation, the study team will contact the candidates and invite them to participate in the study. The investigators will explain in detail the hypothesis and objectives of the study, the methods of obtaining a dietary log and will answer all questions asked by the candidate. No HPI will be obtained in this phone call.

A screening and consent signing visit will be scheduled within 2 weeks after the phone call.

HIPPA waiver authorization to identify and contact the candidates is submitted (see attached).

Step 2: Screening and consent visit:

A face-to-face interview (60 minutes): This interview will be held within 1-2 weeks after “phone call 1.” During this interview, a detailed review of the study design, methods and goal will be provided and explained to the candidates. If the subject agrees to participate in the study, and to ensure compliance with HIPPA regulation, he/she will be asked to read/sign the consent form before obtaining any HPI. Signing the consent form does not mean that the subject is enrolled in the study. After signing the consent form, eligibility screen will be conducted and the subject will be enrolled in the study if eligible.

A review of medical history and medication to evaluate for eligibility will take place after signing the consent form.

Candidates will provide the dietary log and discuss it with the interviewer.

Candidates will be given consenting review/survey document (see attached) to answer to ensure full understanding of the study and acceptance to participate. All candidates will be provided with the appropriate tools to obtain the stool and urine samples (disposable: two ice packs, a box, two tubes, and 24 hour urine collection container).

Dietary evaluation: A dietitian will review the de-identified diet log and estimate the daily AGEs consumption.

Phone call 2: All candidates will be contacted within one week after the screening and consent signing visit to inform them about their eligibility to participate in the study. Candidates who are eligible from the medical history and medication perspective, and who consume a high AGE diet will be invited to participate in the study. A study first visit will be scheduled within 2 weeks and during their regular monthly dialysis visit. Candidates eligible to participate will be instructed to obtain the stool and urine samples and bring the samples to the study first visit.

**Step 2: first visit:**

Enrollment: At this point, candidates are officially enrolled in the study. . Patients on PD are seen by their primary nephrologist every month and blood tests are obtained monthly to evaluate dialysis efficacy and other parameters in this population (standard treatment for ESRD patients on PD).

The first visit will be scheduled to take place during one of the regular monthly dialysis visit, and the study blood samples will be obtained in addition to the blood samples obtained in the regular monthly visit.

Medical evaluation: This will take place during the PD monthly visit. Vital sign measurements and physical examination will be conducted as part of the standard of care, and reviewed by the investigators.

Diet evaluation: Candidates will bring detailed, accurate 3 day diet log for the nutritionist to evaluate.

Sample collection: Stool sample will be obtained and immediately stored in -80C at Annenberg building, floor 23 [name] lab. A total of 45 ml (three tablespoons) will be obtained during this visit. 15 ml (one tablespoon) will be sent to the hospital laboratory to evaluate dialysis parameters as the standard of care. An extra blood sample [30 ml (two tablespoons)] will be obtained for the research study. Blood will be centrifuged to separate supernatant and mononuclear cells and both fractions will be immediately stored in -80C at Annenberg building, floor 23 ([name] lab). 24 hour urine samples will be obtained during this meeting and immediately stored at -80C at Annenberg building, floor 23 [name] lab (see paragraph f for details). Candidates will be given another set of sample collection tools (disposable: two ice packs, a box, two tubes, and urine collection container) to bring in the second visit.

Skin AGE measurement: Measurement of AGE levels in the skin will be done using an AGE reader. This AGE reader provides a non-invasive cardiovascular risk assessment by illuminating the skin of the forearm. The skin AGEs will emit a light that is detected by the AGE reader. The test will last about 10 seconds.

Randomization: Candidates will be randomly assigned to either continue the same diet [G1], or switch to low AGE diet [G2].

Diet education (30 minutes): The study dietitian will meet with both groups and instruct them in regards to food preparation and its content of AGE. Handouts will be given to both groups (see attached).

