**Step 3: Phone calls follow up: (15 minutes)**

The study team will contact both groups twice weekly and take a brief diet evaluation to assess the AGE content of their diet and compliance with the protocol.

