**Step 4: final evaluation:**

Visit: This visit will take place one month after the first visit (enrollment and randomization visit). This visit will be scheduled to take place during the regular monthly dialysis visit, and the study blood samples will be obtained in addition to the blood samples obtained in the regular monthly visit

Diet evaluation: Candidates will bring detailed, accurate 3 days diet log for the nutritionist to evaluate.

Sample collection: Stool sample will be obtained and immediately stored in -80C at Annenberg building, floor 23 [name] lab. A total of 45 ml (three tablespoons) will be obtained during this visit. 15 ml (one tablespoon) will be sent to the hospital laboratory to evaluate dialysis parameters as the standard of care. An extra blood sample [30 ml (two tablespoons)] will be obtained for the research study. Blood will be centrifuged to separate supernatant and mononuclear cells and both fractions will be immediately stored in -80C at Annenberg building, floor 23 [name] lab. 24 hour urine samples will be obtained during this meeting and immediately stored in -80C at Annenberg building, floor 23 [name] lab.

Skin AGE measurement: Measurement of AGE levels in the skin will be done using an AGE reader. This AGE reader provides a non-invasive cardiovascular risk assessment by illuminating the skin of the forearm. The skin AGEs will emit a light that is detected by the AGE reader. The test will last about 10 seconds.

The expected duration of enrollment is **1** year.

The estimated date for the investigators to complete this study is 12/31/2016

- 1. Study Endpoints

Primary Endpoint: Change of gut microbiota after intervention.

Secondary Endpoint: Inflammatory and metabolic marker changes after intervention.

Safety endpoint: Candidates will be asked to either continue with their regular diet, or asked to cook their food in a different way, mainly boiling instead of frying/grilling. All cooking methods and measures to decrease AGE in diet are considered universally safe and are routinely recommended to the general population regardless of their medical conditions.

- 1. Procedures Involved in the Human Research

An initial phone interview will be conducted to invite potential study candidates to participate.

Face-to-face interviews will be performed to obtain consent and medical history as well as and provide training on recording dietary log. Stool, urine and blood samples will be obtained during both meetings.

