Withdrawal without subject’s consent: The study doctor, the sponsor or the institution may stop a subject’s involvement in this research study at any time without their consent. This may be because the research study is being stopped, the instructions of the study team have not been followed, the investigator believes it is in their best interest, or for any other reason. If specimens or data have been stored as part of the research study, they too can be destroyed without their consent.

1. Risks to Subjects

There are no known risks associated with low AGE diet. If participants are randomized to the high AGE diet (usual diet), they are not going to change their diet, and then the risks of maintaining that diet remain the same.

Qualified staff will draw blood using standard sterile equipment. Some people may experience a small amount of pain. On rare occasions, minor bruising may occur. These effects will self-resolve within hours or days. Occasionally, people feel faint or faint after blood draws.

Participants will be asked to bring a 24-hour urine and stool collection for 2 visits, which may create some inconvenience.

There are no risks associated with the AGE reader which only uses a light source to illuminate AGEs in the skin.

We cannot identify any physical or social risks for study participants.

There is a slight concern about possible lost of earnings during the study visit; however, the subject will determine and decide if participating in the study is more important/beneficial then earning wages.

There always exists the potential for loss of private information; however, there are procedures in place to minimize this risk.

1. Provisions for Research Related Injury

All subjects who will experience any side effect that is thought to be secondary to their participation in this study will be provided with all the medical or psychological resources they might need. Subjects with any kind of side effect should contact the study team.

1. Potential Benefits to Subjects

Participants are not expected to get any benefit from taking part in this research.  Although there is no direct benefit to participants in this study, we hope the results will help us to better understand the influence of dietary factors in the progression of the kidney disease. Therefore, we believe the risk/benefit ratio of this research favors the benefits.

1. Provisions to Protect the Privacy Interests of Subjects

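### Both arms are taught about food preparation and AGE content right after randomisation, so the usual-diet controls could drift towards the intervention and weaken the contrast

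*Protocol*

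**What the plan says.** The Protocol's Number of Subjects section separates the arms clearly: "G1: 15 patients will continue their original diet", whereas "G2: 15 patients will be instructed to initiate a low AGE diet". Risks to Subjects repeats the assumption for those randomised to the usual diet: "they are not going to change their diet".

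The safety paragraph of Study Endpoints shows what the intervention consists of. Those not continuing their regular diet are "asked to cook their food in a different way, mainly boiling instead of frying/grilling". The text mentions no supplied food, so the intervention is delivered by instruction.

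In Study Timelines, Step 2 (first visit), the item directly after Randomization is a 30-minute Diet education session: "The study dietitian will meet with both groups and instruct them in regards to food preparation and its content of AGE". The next sentence provides handouts to both groups and refers to an attachment. No arm-specific content is described for the session or the handouts.

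Step 3 adds follow-up calls: "The study team will contact both groups twice weekly and take a brief diet evaluation to assess the AGE content of their diet". The same sentence gives compliance with the protocol as a second purpose of these calls.

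**The concern.** The trial compares continuing a high-AGE diet with switching to a low-AGE one. That comparison depends on G1's diet staying where it was. Teaching G1 how food preparation relates to AGE content gives controls the knowledge by which G2 is supposed to change.

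Several features make a response by controls plausible:

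- The data and safety monitoring plan describes the study as open-label.
- Step 1 has the investigators explain the hypothesis in detail to each candidate, and that hypothesis is that a low-AGE diet is better for the gut microbiota.
- The inclusion criteria require an estimated intake above 12 AGE Eq/day, so every control has room to reduce.
- Study Endpoints presents AGE-lowering cooking as universally safe and routinely recommended, so nothing in the text would discourage a taught control from adopting it.

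If controls do reduce their AGE intake, the between-group difference in the primary endpoint, change of gut microbiota, is biased towards zero. With 15 randomised per arm there is little room for that loss.

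**Working it through.** **Side-by-side reading.** Three places in the Protocol (Number of Subjects, the Randomization item, Risks to Subjects) define G1 by an unchanged diet. One place (Diet education) has the dietitian instruct G1 on the topic that makes up the intervention in Study Endpoints. The Protocol does not say what G1 is to do with that instruction, nor that it differs from G2's. As written, the passages do not fit together.

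**Illustration of size.** The Protocol has no power figure to reproduce; it says that a power analysis cannot be performed. The inputs are:

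- Completers per arm: 15 × (1 − 0.20) = 12, from the enrolment and dropout rate in Number of Subjects.
- Test: two-sample t, two-sided alpha 0.05 (assumed).
- Undiluted effect: the standardised difference giving 80% power at n = 12 per arm, which is 1.197, about 1.2 SD (assumed).
- c: the fraction of G2's AGE reduction that controls also make (assumed; the documents give none).
- Effect proportional to AGE reduction (assumed), so the contrast becomes 1.197 × (1 − c).

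Non-centrality = 1.197 × (1 − c) × √(12/2) = 2.93 × (1 − c), with 22 degrees of freedom and critical value 2.07. The sample size needed to hold power grows by 1/(1 − c)².

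| c | Contrast (SD) | Non-centrality | Power | Sample-size factor | n per arm to match 12 |
|---|---|---|---|---|---|
| 0 | 1.20 | 2.93 | 80% | 1 | 12 |
| 0.10 | 1.08 | 2.64 | 71% | 1.23 | 15 |
| 0.25 | 0.90 | 2.20 | 56% | 1.78 | 22 |
| 0.50 | 0.60 | 1.47 | 29% | 4.00 | 48 |

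With 10 or 15 per arm, the effects giving 80% power are about 1.33 and 1.06 SD. Starting from those, power falls by the same amounts, because each row begins at 80%. The sample-size factor does not depend on n.

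**The case against.** The strongest reply is that the text does not say G1 is asked to cook differently. The Diet education sentence can be read as one dietitian meeting each group about its own assigned diet, and equal contact time is a recognised way to match attention between arms. The handouts are an attachment that is not at hand and may differ by arm. All of this is possible. What remains is that the Protocol gives one description of the teaching for both groups and states no difference in content.

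Three stronger readings are tempting, and the documents do not support them:

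- *Controls do change their diet.* Nothing shows this. The text shows a mechanism with a predictable direction, not its occurrence or its size.
- *The calls contaminate G1 as much as the teaching does.* The calls also check compliance, which for G1 means keeping the original diet. They may hold controls in place as easily as shift them.
- *A null result could not be told apart from contamination.* G1's exposure is measured: 3-day diet logs and skin AGE readings at both visits, AGE assays in the serum and urine collected at both visits, and the dietary checks in the calls. Drift could be seen and a null result examined for it. These measures cannot prevent drift or restore the lost contrast.

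The nonadherence rule in item 5 of the monitoring plan shows that diet is watched, but it does not say how it applies to G1. If it were used on controls who reduce their AGE intake, drift would become exclusion after randomisation from a 15-person arm.

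The power figures are also open to challenge. This is a one-month pilot that claims no power, and change of gut microbiota is not defined as a single continuous variable. That objection stands, so the figures only illustrate how sensitive a small comparison is to dilution.

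**Conclusion.** The point holds as a design risk that should be fixed, not as a demonstrated bias or a must-fix fault. The Diet education paragraph conflicts with the definition of G1 and could bring the control diet closer to the intervention. The resulting bias would be towards zero, provided that controls respond by lowering AGE intake and that the microbiota effect follows AGE intake. The amount is unknown. Under the stated assumptions the loss runs from modest (power 71% if controls make a tenth of G2's change) to severe (29% if they make half). The case rests mainly on the teaching, with support from the handouts as far as the text describes them. The calls are secondary.

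**What to change.** Reconcile Diet education with Number of Subjects and Risks to Subjects:

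- Give the AGE content, the cooking-method instruction and the AGE handouts to G2 only.
- Give G1 a session of equal length on completing the 3-day log and keeping its usual diet, and offer it the AGE handouts after the final visit.
- If arm-specific sessions or handouts already exist, say so in the paragraph; one sentence would do.
- As a secondary change, keep the twice-weekly calls at equal frequency in both arms, preferably as a neutral food recall that staff score for AGE content afterwards.

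The cost is a revised session outline, handout plan and call script, with the same dietitian and the same contact time. There are two limits. Session content will differ between arms, although contact time stays matched. G1 will also still know the hypothesis from recruitment and consent, so the change reduces the risk without removing it. It needs to be made before enrolment, because drift during the month cannot be undone at analysis.
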